## Abstract

**Background:**

Preterm infants have a risk of health and developmental problems emerging after discharge. This indicates the need for a comprehensive follow-up to enable early identification of these problems. In this paper, we introduce a follow-up tool “ePIPARI – web-based follow-up for preterm infants”. Our future aim is to investigate whether ePIPARI is a feasible tool in the follow-up of preterm infants and whether it can identify children and parents in need of clinical interventions.

**Methods:**

ePIPARI includes eight assessment points (at term age and at 1, 2, 4, 8, 12, 18, and 24 months of corrected age) when the child´s health and growth, eating and feeding, neurodevelopment, and parental well-being are evaluated. ePIPARI consists of several widely used, standardized questionnaires, in addition to questions typically presented to parents in clinical follow-up visits. It also provides video guidance and written information about age-appropriate neurodevelopment for the parents.

Parents of children born before 34 weeks of gestation during years 2019–2022 are being invited to participate in the ePIPARI study, in which web-based follow-up with ePIPARI is compared to clinical follow-up. In addition, the parents of children born before 32 weeks of gestation, who reached the corrected age of two years during 2019–2021 were invited to participate for the assessment point of 24 months of ePIPARI. The parents are asked to fill in the online questionnaires two weeks prior to each clinical follow-up visit.

**Discussion:**

The web-based tool, ePIPARI, was developed to acquire a sensitive and specific tool to detect infants and parents in need of further support and clinical interventions. This tool could allow individualized adjustments of the frequency and content of the clinical visits.

**Trial registration:**

ClinicalTrials.cov, NCT05238168. Registered 11 April 2022 – Retrospectively registered.

## Background

Advances in perinatal and neonatal care have led to better survival of preterm infants from early gestational weeks [1, 2], which have led to increased need for neonatal follow-up services. Preterm birth is associated with problems in later growth, health, and neurodevelopment [3–6]. Parents of preterm infants also have an increased risk for stress, anxiety, and depression [7–9] that may negatively affect their child’s well-being and development throughout childhood. Literature suggests that especially very preterm (< 32 weeks’ gestation) infants should have careful follow-up for early identification of prematurity-related problems [10, 11]. However, also infants born moderate and late preterm (33 − 36 weeks of gestation) have shown to be in a higher risk of long-term health and neurodevelopmental sequelae compared with infants born at term [12, 13].

The European Foundation for the Care of Newborn Infants has recently recommended the follow-up of very preterm children with standardized assessments of neurodevelopment and behavior at 2 years of age and at transition to school [14]. Targeted screening of parental mental health through regular follow-up visits is also included in recommendation [14]. The Swedish national recommendation includes follow-ups at 2 and 5.5 years of age for extremely preterm infants born below 28 weeks of gestation and for all preterm infants with brain injuries, severe morbidity, or severe growth retardation [15]. The National Institute for Health and Care Excellence guidelines for the United Kingdom recommend a two-year follow-up for all children born below 30 weeks of gestation. In addition, children born between 30 and 36 weeks of gestation should be followed if they have additional risk factors of abnormal development [16]. Although the importance of neonatal follow-up is internationally recognized, there is a need for structured evidence based multidisciplinary follow up practices. It is important to develop evidence-based follow-up programs to improve cost-efficiently the quality of the follow-up of preterm infants and to create opportunities for a more uniform follow-up practice. Systematic follow-up and timely interventions make it possible to target the limited resources and the services effectively to those children and families who need them most.

eHealth Screening and Support tools have been suggested as being useful in early intervention and personalised support [17, 18] and could facilitate the follow-up programs of preterm infants with risks. Internet-based interventions and digital materials have shown to be beneficial in paediatric mental health problems and in parental support [19–22]. The use of a range of approaches for example in intervention and supporting families is also recommended in national recommendations for premature infants [14, 16]. As there are no previous reports on web-based follow-up tools for preterm infants that cover all aspects of developmental follow-up, that we are aware of, ePIPARI- a follow-up tool for preterm children was developed in Turku University Hospital based on clinical knowledge and relevant international literature as well as expertise gained from the PIPARI-study (The Development and Functioning of Very Low Birth Weight Infants from Infancy to School Age) (www.utu.fi/pipari).

Our aim was to develop a web-based tool that could supplement the follow-up and family intervention services of preterm infants so that different needs and health care resources could be met sufficiently. The goal of web-based tool, ePIPARI, is to target the resources and the services cost- effectively to those preterm children and families who need them most, and also enable the follow-up of low risk late preterm infants otherwise left out of the clinical follow-up due to limited resources. The purpose is to enhance the follow-up through web-based monitoring; reduce the amount of unnecessary routine visits for very preterm children doing well and also identify those in need for additional visits and interventions. Also, by reducing the amount of unnecessary routine visits, digital follow-up could also be offered for all late preterm infants and according to the answers in the ePIPARI, those children and families in need can be called for clinical visits. For the clinicians, ePIPARI provides an additional tool to obtain information e.g. about parental well-being and the child’s socio-emotional development indicating increased risk for later psychiatric symptoms. Previous studies suggest that it is easier for clients and parents to report their sensitive information without face-to-face contact [17, 18]. Obtaining this information allows early intervention and further guidance.

In this paper, we introduce our web-based follow-up tool ePIPARI and the study protocol for evaluation. To evaluate the feasibility and performance of ePIPARI we designed a prospective study in which web-based follow-up with ePIPARI is compared to clinical follow-up.

## Methods

### Aims

The aim of this prospective study is to investigate whether the ePIPARI is a feasible and valid tool for follow-up of preterm infants in identifying children and families in need of further clinical interventions or support compared to clinical follow-up. We hypothesize that 1) ePIPARI is a feasible tool for the follow-up of preterm infants and their parents, and 2) it is comparable to routine clinical follow-up in recognizing children and parents in need for requiring interventions.

### The structure of ePIPARI

ePIPARI is a digital follow-up tool on a web-based platform. It provides comprehensive follow-up for preterm children and their parents from term age until 2 years of corrected age. ePIPARI-follow-up tool was developed by the multidisciplinary PIPARI Study group and the staff of the Pediatric Unit of Turku University Hospital and is based on international recommendations and relevant literature. In addition, clinical knowledge and expertise gained from the PIPARI-study have been utilized in the development of the tool. The PIPARI Study group consist of researchers and experts from different disciplines, including pediatric and adolescent medicine, nursing science, pediatric neurology, psychology, neuropsychology, speech-language pathology, public health, psychiatry, physiotherapy and neuroradiology. The content and questionnaires of each time point in ePIPARI were developed and planned in collaboration with this multidisciplinary team. The permission to use standardized assessments and copyright-related issues has been taken into account. In addition, the nurses of Preterm Infant Follow-Up Clinic and Neonatal Intensive Care of Unit participated in planning the content. The technical implementation of the web-based material was carried out by Kaiku Health-company, whose web-based platform was already in use at Turku University Hospital in Pediatric Oncology Unit.

ePIPARI includes eight assessment points: term age, 1, 2, 4, 8, 12, 18 and 24 months of corrected age. It evaluates the child´s health and growth, eating and feeding, neurodevelopment (development of motor skills, language, cognition, behavior, and socials skills) and family wellbeing (parental depression and marital satisfaction) (Table 1). Responses are classified for typical development, growth and behavior or responses of concern using different thresholds or a traffic light model. Widely used standardized questionnaires, and age-appropriate clinical questions are used (Table 2). ePIPARI also provides videos of health and typical development, as well as written information on how to support a child’s development and how to get help with concerns related to parenting or child’s developmental problems.

**Table 1 Tab1:** ePIPARI – Web-based follow-up of preterm infants. Age points (corrected age) and topics

	Term age	1 month	2 months	4 months	8 months	12 months	18 months	24 months
Health	x	x	x	x	x	x	x	x
Growth	x	x	x	x	x	x	x	x
Feeding and eating	x	x	x	x	x	x	x	x
Motor development			x	x	x	x	x	x
Language development						x	(x)	x
Cognitive development								x
Behavior and self regulation							x^a^	x
Social relationships							x^a^	x
Interaction and attachment				x	x			x
Parental well-being, depression and marital satisfaction					x^a^	x^a^		

^a^questionnaires for both parents separately

(x) for children scored below the 10^th^ percentile value of the norming sample of the FinCDI-SF or FinCSBS-ITC at 12 months of corrected age

**Table 2 Tab2:** ePIPARI—Web-based follow-up of preterm infants. Assessment methods

Language development	Finnish version of the Infant–Toddler Checklist of the Communication and Symbolic Behavior Scales Development Profile (FinCSBS-ITC) The Finnish Short Version of the MacArthur Communicative Developmental Inventories (FinCDI-SF)
Cognitive development	Parent Report of Children’s Abilities-Revised for preterm infants (PARCA-R)
Behavior and Self regulation	Brief Infant–Toddler Social and Emotional Assessment (BITSEA)
Social relationships	Brief Infant–Toddler Social and Emotional Assessment (BITSEA)
Parental well-being and functioning	Edinburgh Postnatal Depression Scale (EPDS) Revised Dyadic Adjustment Scales (RDAS)

#### Measures of the web-based follow-up

##### Health and growth

At every age-point there are general questions of health, growth, nutrition (type of milk, dietary supplements, solid food, vitamins), eating difficulties and medications, bowel function, skincare, vision and hearing and sleeping. Growth is evaluated by requesting the growth measures (weight, length, head circumference) from the last visit to the public well-baby clinic. Growth is evaluated using the Finnish age and sex specific growth charts and the growth screening program. General health/illness is evaluated by questions on any possible underlying illnesses, acute and previous infections, and different symptoms, for example, difficulties in breathing, posseting, constipation, and crying. Clinical problems are evaluated with categories of concern. Information on the sleeping habits of the child is also asked at each age point. A Patient and Public Involvement approach is included by asking the parents questions about concerns related to their child and opinions on the survey; “What would you like us to ask?” and “Did you find these questions relevant?”.

#### Neurodevelopment

*Motor development* is outlined with questions related to age-appropriate motor development at each age point beginning from 2 months of corrected age. Parents are asked for example if the child is able to maintain her/his head upright, whether the child uses both hands and legs equally, and what kind of postures and motility is typical for the child. The tutorial videos on ePIPARI are offered to help parents to answer the questions about motor skills. If there is any deviation from the expected age-appropriate level, additional detailed follow-up questions then follow. Concerns about motor development are evaluated using a traffic light model for each item, where green indicates that child is developing typically, yellow means a possible risk, and red a clear risk of developmental problems.

Information on the emerging *language and communication ability* is collected at 12 and at 24 months of corrected age using the Finnish short form versions of MacArthur Communicative Development Inventories, FinCDI-SF [23–25] and different composites of the Finnish version of the Infant–Toddler Checklist of the Communication and Symbolic Behavior Scales Development Profile (FinCSBS-ITC) [26, 27]. Both methods have been adjusted using norming and validated for the Finnish population, and they provide information on early receptive and expressive lexical development and early communicative behavior (i.e. expression of emotions, use of gaze, communication ability, gesture, and object use). The cut-off points of the norming population for these methods (the weakest 10^th^ percentile) are used to identify children at risk for language development and communication.

*Cognitive development is* assessed at 2 years of corrected age using a Finnish translation of the original English Parent Report of Children’s Abilities-Revised questionnaire (PARCA-R) validated for premature children [28, 29]. The original PARCA-R is a parent questionnaire concerning children’s nonverbal cognitive and language development at 2 years of age. It has been shown to be sensitive and specific in identifying a neurodevelopmental delay in children born preterm [29, 30]. In this protocol only the section assessing nonverbal cognition consisting of 34 items is used. The items are being summed to give a nonverbal cognitive subscale score. The cut-off point of 24 points (the weakest 10^th^ percentile) is used to identify children with developmental delay. The original PARCA-R version also includes a short form version of the Communicative Development Inventories in the language in question, and some items assessing language structures. In ePIPARI, the Finnish short form versions of MacArthur Communicative Development Inventories (FinCDI- SF) is used to collect information on lexical ability at two years of age. This information can be used together with nonverbal cognitive subscale.

*Behavior and social skills* are evaluated at 24 months of corrected age using the Brief Infant–Toddler Social and Emotional Assessment (BITSEA)—questionnaire including 42 items [31]. Based on the items, five subscales are formed; *externalizing subscale* e.g. aggression, overactivity, *internalizing subscal*e e.g. shyness, anxiety, *dysregulation problems subscale e.g*. sleeping, eating, and emotion regulation problems and *maladaptive behaviors subscales* e.g. behaviors related to autism spectrum disorder and *social competence* e.g. prosocial peer relations, empathy, play skills and social relatedness. The questions and interpretation of the results are separated into problem and competence categories. The first four subscales are combined to form a total problems score. The problem total cut-off score is set at the 25^th^ percentile, and the competence total cut-off score at the 15^th^ percentile and these are used to recognize the child’s risk of behavioral and social problems.

#### Family well-being

*Parental sleep quality* is evaluated at each age point, but a more detailed questionnaire is sent to both parents when the child is at 8 months of corrected age. The quality of parents’ sleep at 8 months of corrected age is assessed using 8 items extracted from the original Basic Nordic Sleep Questionnaire (BNSQ) [32, 33]. The *family`s well-being* is examined by asking about the social support they have received as regards formal or/and informal support, and the help they would like to have to give them more support with everyday life. *Parental depressive symptoms* are assessed separately from both parents when the child is at 8 months and 12 months of corrected age by *the Edinburg Postnatal Depression Scale* [34] which has been widely used to assess maternal depression. A cut-off value of 13 is used. In addition, *marital satisfaction* is assessed with The Revised Dyadic Adjustment Scale, RDAS [35] when the child is at 8 months of corrected age. The RDAS is a shortened version of the Dyadic Adjustment Scale [36]. It consists of 14 items designed to measure adjustment in dyadic relationships on 3 sub-scales: Consensus, Satisfaction and Cohesion.

#### Parent’s user-experience

To study the usability, parents are asked to anonymously complete enquiries about user-experience of the web-based follow- up via email. These enquiries ask parents if it has been very easy, easy, difficult, or very difficult to answer the questions, how time consuming they have found filling in the forms, whether the material provided by the service has been useful, and if they have experienced any benefits. Parents are also asked to give general feedback and improvement suggestions. The ePIPARI follow-up protocol can be improved during the study based on the experiences of the families or researchers.

### Information of routine follow-up as comparison

The routine follow-up of preterm infants in Turku University hospital serves as a comparison for the performance of ePIPARI. The children born < 32 weeks or ≤ 1500 g are routinely followed systematically until the corrected age of two years, while the infants born between 32 and 34 weeks of gestation (and ≤ 1500 g) participate in routine follow-up visits at least at 2, 4 and 8 months of corrected age and the follow-up continues until they are able to stand up independently (usually until 1 year of corrected age). The follow-up focuses on identifying issues that require clinical evaluation, such as concerns about growth and feeding, neurodevelopment, and parental wellbeing. The structure of the routine follow-up is presented in Table 3.

**Table 3 Tab3:** Clinical follow-up schedule for very preterm infants at the University Hospital of Turku, Finland

Assessment methods and examinations	Term age	1 month	2^a^ months	4^a^ months	8 months	12^a^ months	24 months
Clinical examination by pediatrician and physiotherapist	x	x	x	x	x	x	x
Growth: weight, length, and head circumference by registered nurse	x	x	x	x	x	x	x
Dubowitz neurological examination by physiotherapist	x	x	x	x			
Hammersmith Infant Neurological Examination by physiotherapist						x	
Finnish Long Form Version of the MacArthur Communicative Developmental Inventories (questionnaire)						x	
Bayley Scales III (Infant and Toddler Development) by psychologist and physiotherapist							x
Edinburgh Postnatal Depression Scale (EPDS) for both parents (questionnaire)				x			
Magnetic Resonance Imaging of the brain	x						
Brainstem Auditory Evoked Potential		x					

In addition to the schedule above, the follow up includes ophthalmological examination at 3–3,5 years of age. All ages are corrected for prematurity

^a^for infants born at gestational weeks 32–34 GA

### Participants and recruitment procedure

The recruitment process is ongoing. Parents of all preterm children, who meet the inclusion criteria during 4/2019–12/2022 are approached before discharge and asked to participate in the “ePIPARI—web-based follow-up of preterm infants”. The inclusion criteria for the infants and the parents are 1) infant is born before 34 gestational weeks, 2) infants have systematic developmental follow-up in pediatric unit in Turku University Hospital and 3) parents speak Finnish, Swedish or English. Inclusion criteria for participating only in the two-year corrected age was that the child is born before 32 gestational weeks during 2019–2021. We excluded infants, who didn’t have clinical follow-up in Turku University Hospital and parents, who couldn`t speak Finnish, Swedish or English.

Recruitment takes place in the neonatal intensive care unit by a registered nurse or a PhD-student ([name]) and the link for registration is sent to the parents’ email. After registration, parents log into ePIPARI via email or via a Mobile App by using a secure strong recognition. Advice and support for logging in is provided by a nurse before discharge. All preterm born children have the routine follow-ups regardless of their participation in the study.

The ongoing data collecting process is as follows: A digital invitation to complete the age-point specific questionnaires is sent two weeks prior to each age-point to parents’ email or to Mobile App. Parents can complete the questionnaires together or only by another, but queries related to family well-being are sent to both parents separately (Table 1). Reminders are sent if the questionnaires are not filled in. The aim is for the questionnaires to be completed before the clinical follow-up visits and so that afterwards the answers can be compared to the (written) medical records made in the clinical visits. The staff of the Pediatric unit will be blinded for the data of the ePIPARI so that it does not affect their assessment during clinical visits. Experienced medical doctors evaluate the answers of the questionnaires at two weeks intervals and estimate the amount of concern based on the responses and pre-set cut-off points. If there is significant concern that was not evident during the clinical follow-up visit, the medical doctor contacts the family or staff of the neonatal follow-up clinic.

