### Plan for statistical analysis

Data will be presented using descriptive statistics: mean values (SD) for normally distributed data, median (range/min, max) for data that are not normally distributed, and counts with percentages for categorical data.

The main comparison between digital assessment and clinical evaluation for each timepoint will be done with McNemar test (binary categorization) or Bowker test (more than two categories) for disagreement. Digital assessment will be categorized with different thresholds or a traffic light model (“child is developing typically”, “a possible risk or a clear risk”) and clinical assessment will be categorized to categories: “no concern”, “concerns requiring clinical intervention including specialist consultations, further investigations, additional controls/follow-up visits, prescription medication or supplements or referral for treatment or therapy”. Also, agreement and it’s 95% confidence interval will be calculated. Furthermore, sensitivity, specificity, positive and negative predictive values will be calculated (compared to clinical assessment).

Pearson’s or Spearman’s correlation coefficients will be generated to evaluate the linear relation between continuous variables.

In addition, to study the association between predictor and response variables within ePipari or clinical assessment visits, linear models or logistic regression models can be built up. The effect of confounding factors (such as socio-economic status, pregnancy week when child was born) will be taken into account, as appropriate. For those measurements which are evaluate repeatable, linear mixed models suitable for repeated measurements will be used.

Statistical analyses will be performed using SPSS version 29 or later or SAS System, version 9.4 for Windows or later. Two-sided p-value < 0.05 will be considered as statistically significant. Confidence intervals of 95% will be calculated, especially for feasibility part of the study.

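### Concerns seen only by ePIPARI are passed to the family or clinic, so blinding of the clinical reference may fail at a contacted child's later visits, which the plan still compares

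*Protocol article*

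**What the plan says.** Four statements under Participants and recruitment procedure matter.

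- Blinding of the reference: "The staff of the Pediatric unit will be blinded for the data of the ePIPARI so that it does not affect their assessment" at the visits.
- Rating of ePIPARI: "Experienced medical doctors evaluate the answers of the questionnaires at two weeks intervals and estimate the amount of concern", and they do so "based on the responses and pre-set cut-off points".
- Contact rule: "If there is significant concern that was not evident during the clinical follow-up visit, the medical doctor contacts the family or staff". The staff meant are those of the neonatal follow-up clinic.
- Timing: "The aim is for the questionnaires to be completed before the clinical follow-up visits", and "Reminders are sent if the questionnaires are not filled in". No closing date is given.

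Under Plan for statistical analysis, the main comparison between digital and "clinical evaluation for each timepoint will be done with McNemar test" (or Bowker's test for more than two categories). Sensitivity, specificity and predictive values take the clinical assessment as the standard. Under The evaluation of feasibility and performance, a clinical concern includes extra visits, consultations and referrals.

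**The concern.** The blinding statement and the contact rule concern the same clinic. A contact arises when ePIPARI raises a significant concern and the visit did not. When the clinic, or a parent who then tells the clinic, carries that information into the next visit, the reference assessment is no longer independent of the test being evaluated.

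The effect is selective. It falls on ePIPARI-positive, clinic-negative children, the cell that determines specificity and positive predictive value and is one of McNemar's two discordant cells. A contact can also lead to an extra visit or referral, which itself counts as a clinical concern.

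Two smaller openings sit beside it. Someone on the ePIPARI side must know the visit result to judge that a concern was missed there, and no reading order is stated. Completion before the visit is only an aim, so a parent could answer after hearing the clinician's view.

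The study is meant to show whether ePIPARI is comparable with routine follow-up and could reduce routine visits safely. Accuracy figures helped by feedback from the tool itself would mislead that decision.

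**Working it through.** **Inputs.** From Sample size and statistical power: proportions 42% and 77%, paired correlation 0.35, two-sided 5%, power 80%, N = 26. From The structure of ePIPARI: eight age points, hence seven rounds before 24 months. Contact rates and the carry-over share f are not in the documents and are assumptions.

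**1. The plan's own figure.**
- Both positive: 0.42×0.77 + 0.35×√(0.42×0.58×0.77×0.23) = 0.396.
- Discordant cells: 0.42 − 0.396 = 0.024 and 0.77 − 0.396 = 0.374, total 0.398. Both negative: 0.206.
- McNemar n = [1.960×√0.398 + 0.842×√(0.398 − 0.35²)]² / 0.35² = 22.98.
- With continuity correction: (22.98/4)×[1 + √(1 + 2/(22.98×0.35))]² = 25.76, rounded up to 26. The stated N is reproduced, and nothing below changes it.

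**2. Who is exposed.** A contact follows the visit that missed the concern, so the pair at that age is still blind. The first age point has no earlier round. Nor does the cohort invited only for 24 months (Abstract, Methods). Everyone else is potentially exposed from the second age point on.

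**3. How many could be contacted before 24 months.** With rate p per round, independent across rounds, the share ever contacted is 1 − (1 − p)^k.
- Seven rounds: 13%, 30% and 52% for p = 2%, 5% and 10%.
- Six rounds (Table 3 has no clinic visit at 18 months): 11%, 26% and 47%.

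Recurrence of concerns in the same children would lower these shares.

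**4. Effect if a share f of ePIPARI-only pairs (cell w) becomes positive on both sides.** With n the both-negative cell: agreement = 0.396 + f·w + n; specificity = n/[n + (1 − f)w]; PPV = (0.396 + f·w)/(0.396 + w).

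| | f = 0 | f = 0.25 | f = 0.5 |
|---|---|---|---|
| ePIPARI 42% (w = 0.024): agreement | 60.2% | 60.8% | 61.4% |
| specificity | 89.6% | 92.0% | 94.5% |
| PPV | 94.3% | 95.7% | 97.2% |
| ePIPARI 77% (w = 0.374): agreement | 60.2% | 69.6% | 78.9% |
| specificity | 35.5% | 42.4% | 52.4% |
| PPV | 51.4% | 63.6% | 75.7% |

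The sample-size sentence names web-based first and 42% first, so the upper block follows its order. There the marginal gap widens from 35.0 to 36.2 points at f = 0.5. In the lower block it shrinks to 16.3.

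**5. A different path.** Suppose the contacted concern later shows only on the clinic side. Agreement stays at 0.396 + 0.206 = 60.2%. Sensitivity = 0.396/(clinic proportion + f·w). With ePIPARI at 77% it falls from 94.3% to 77.1% (f = 0.25) or 65.3% (f = 0.5). With ePIPARI at 42% it falls from 51.4% to 50.7% (f = 0.5).

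**6. Late forms.** If a share g of discordant pairs moved to the clinic's result, agreement would be 64.2%, 70.2% and 80.1% for g = 0.10, 0.25 and 0.5. This is illustration only, because the text does not say how late forms are handled.

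**The case against.** The strongest reply is that the contact rule does less damage than it seems. It operates after the visit, so same-age pairs are intact. It goes to the family or the staff, so the clinic is not always told. A clinic that is told knows one past concern, not the answers to later questionnaires. Some content is new at the end: cognition is asked only at 24 months. The comparator is already taken from written visit records. All of this stands, and it limits the size of the problem. It does not reconcile the blinding statement with the contact rule for a contacted child's later visits.

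Four stronger readings are tempting, and the documents do not support them.

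- *That agreement is inflated as a matter of fact.* Step 5 shows a path on which agreement does not move and sensitivity falls. With the labels as written, step 4 moves agreement by only about 1 point.
- *That late questionnaires are counted.* The article neither includes nor excludes them, and an unseen full protocol or SAP may settle it.
- *That ePIPARI is rated with knowledge of the visit.* The rating is said to rest on answers and fixed cut-offs. The visit result is needed only for the contact decision. What remains is that no order of the two steps is stated.
- *That the powered 24-month comparison is wholly compromised.* The 24-month-only cohort has no earlier round.

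It might also seem natural to drop contacted children's later pairs from the main analysis. That would select on earlier disagreement and, if disagreement persists within a child, enrich the remaining set for agreement.

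**Conclusion.** The point holds in limited form. As written, the plan promises a blinded reference, passes selected ePIPARI findings towards that reference, and then compares all age points without separating exposed from unexposed pairs. Agreement, specificity and PPV at later ages may be biased, more likely upward than downward, but neither size nor direction can be fixed from the documents. For f up to 0.5, the shift in agreement runs from nil (step 5) through 1.2 points (ePIPARI 42%) to 18.7 points (ePIPARI 77%). These figures rest on an assumed carry-over share applied to the plan's 24-month inputs, and f = 0.5 is the top of the range examined. They also count every ePIPARI-only flag, whereas contact requires a significant concern, so they lean high. The first age point, the 24-month-only cohort and N = 26 are not affected by the contact rule. Reading order and completion timing are secondary openings of unknown effect.

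**What to change.** Leave contact with families unchanged and alter only recording and analysis.

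- (a) Lock and time-stamp the ePIPARI classification before the clinical record is opened.
- (b) Have the clinical outcome coded from the dated visit note by someone who does not see ePIPARI.
- (c) Log the date of every contact. Keep post-contact pairs in the main analysis and report a sensitivity analysis without them. Show the 24-month-only cohort separately as never exposed.
- (d) Base the main comparison on questionnaires submitted before the visit, and report late ones separately.

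The cost is a time-stamp, a log field and some extra analysis. Setting late forms aside widens the intervals: if 10% were late (assumed), by a factor of 1/√0.90, about 5%. The sensitivity analysis in (c) could be much less precise. Losing 30% or 52% of pairs widens intervals by about 20% or 44% (1/√0.70, 1/√0.48) and would leave about 18 or 12 of 26 pairs, which is a further reason not to make it the main analysis. Data collection is ongoing, and reading order and contacts may not be recoverable unless recorded at the time, so (a) and (c) should start first.
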